## Abstract

**Background:**

Disappointing results from clinical trials of disease-modifying interventions for Alzheimer’s dementia (AD), along with reliable identification of modifiable risk factors in mid life from epidemiological studies, have contributed to calls to invest in risk-reduction interventions. It is also well known that AD-related pathological processes begin more than a decade before the development of clinical signs. These observations suggest that lifestyle interventions might be most effective when targeting non-symptomatic adults at risk of AD. To date, however, the few dementia risk-reduction programs available have targeted individual risk factors and/or were restricted to clinical settings. The current study describes the development of an evidence-based, theoretically-driven multidomain intervention to reduce AD risk in adults at risk.

**Method:**

The design of Body Brain Life (BBL) is a randomized controlled trial (RCT) to evaluate a 12-week online AD risk-reduction intervention. Eligible participants with several modifiable risk factors on the Australian National University (ANU) AD Risk Index (ANU-ADRI) are randomly allocated to an online only group, an online and face-to-face group, or an active control group. We aim to recruit 180 participants, to undergo a comprehensive cognitive and physical assessment at baseline, post-intervention, and 6-month follow-up assessment. The intervention comprises seven online modules (dementia literacy, risk factor education, engagement in physical, social, and cognitive lifestyles, nutrition, and health monitoring) designed using contemporary models of health behavior change.

**Discussion:**

The BBL program is a novel online intervention to reduce the risk of AD in middle-aged adults at risk. The trial is currently under way. It is hypothesized that participants in the intervention arms will make lifestyle changes in several domains, and that this will lead to a reduction in their AD risk profile. We also expect to show that health behavior change is underpinned by changes in psychological determinants of behavior. If successful, the findings will contribute to the development of further dementia risk reduction interventions, and thus contribute to the urgent need to lower dementia risk factors in the population to alter future projections of disease prevalence. Longer follow-up of BBL participants and replications using large samples are required to examine whether reduction in AD risk factors will be associated with reduced prevalence.

**Trial registration:**

Reg. no. ACTRN12612000147886

## Background

As the most common cause of dementia, Alzheimer’s disease (AD) affects approximately 35 million people worldwide, and this will increase with population ageing [1]. There is increasing focus on delaying the onset of AD through intervening to modify risk factors [2,3], and it has recently been estimated that a 10% to 25% reduction in 7 key risk factors could prevent 1.3 million AD cases internationally [2]. To our knowledge only a few prevention trials for Alzheimer’s disease are currently under way, and interventions that could be delivered at the population level (as opposed to interventions conducted in clinical settings) have not yet been developed. The largest ongoing trial of dementia prevention is the Multi-domain Alzheimer Prevention Trial (MAPT), which involves MRIs, fish oil and clinical assessments, and costs millions of dollars. Other randomized controlled trials (RCTs) targeting dementia prevention have either focused on a single risk factor (for example, hypertension) or are clinically based and require full medical assessments and expensive treatment regimes. There is an urgent need to develop population-level, low-cost interventions that will reduce the risk of AD.

The present study builds on our research program on dementia risk reduction that commenced in 2005 and has led to four systematic reviews [4-7], and the development of evidence-based and validated self-report tool for the assessment of risk of AD [8]. We have also examined predictors of conversion to preclinical dementia in our PATH Project [9]. We have designed an intervention study to reduce the risk of AD by concurrently targeting modifiable risk factors in middle-aged adults. The intervention is designed for distribution via the Internet, and hence, may reach a far wider group of individuals within the population than the high-cost medical interventions currently under way.

Risk factors for cardiovascular disease in older persons are well established and include several modifiable lifestyle factors. More recently, converging evidence from large epidemiological studies has confirmed that some of the central modifiable risk factors for cardiovascular disease are also risk factors for AD, the most common cause of dementia in people over 65 years of age. These factors include smoking, alcohol consumption, poor diet, depression, and physical inactivity. Other factors that appear to play a protective role in the prevention of AD, such as engagement in social and cognitively stimulating lifestyles, may play less of a role in the prevention of cardiovascular disease. The proposed trial (reg. no. ACTRN12612000147886) is currently under way in Australia.

### Targeting mid-life adults at risk

To date, most interventions to reduce dementia risk have generally targeted older individuals (>65 years), who are at risk of AD due to the presence of objective or subjective cognitive decline, a positive family history of dementia, or the detection of disease biomarkers. However, it is widely accepted now that pathological processes that lead to the development of clinical AD commence years and even decades before the onset of any detectable clinical symptoms [10]. It has been suggested that intervening at the point at which clinical symptoms become apparent may be too late. In addition, commencing in 2005, a series of systematic reviews by our group has demonstrated the links between several risk factors in mid life and the likelihood of developing dementia later in life [4-7]. Building on our findings and those of other groups, we have recently developed and validated a self-reported measure of AD risk at mid life [8]. Using such a tool in the development of interventions to reduce the prevalence of dementia risk factors in mid life may therefore have far-reaching implications for the incidence of dementia in later life.

### Use of behavior change theory

Although theory-driven interventions have been developed in the context of single risk factors to prevent cardiovascular disease (see, for example, [11]), research into dementia that concurrently targets various risk factors is in its infancy. Existing interventions have not been explicitly developed against a clear theoretical framework of behavior change. However, there is evidence that lifestyle interventions informed by theoretically-driven behavior change models are more successful and lead to stronger and more lasting changes [12]. Consequently, a complex intervention based on an emerging theoretical and empirical model of health-related behavior change [13-15] has been developed for the current project.

### Online delivery

The percentage of interventions developed and delivered over the Internet has grown dramatically over the past decade. Internet-delivered interventions are appealing to public health professionals for several reasons. First and most importantly, online interventions provide the opportunity for large-scale implementation at the population level compared with more traditional face-to-face interventions. Further, although the initial cost associated with setting up such interventions is at times relatively high, their cost effectiveness lies in the relatively small ongoing costs, which coupled with their wide reach has the potential of having large impact [16]. Finally, the ever-increasing sophistication of Internet-based health interventions enables them to become individually tailored [17]. Evidence has emerged in recent years of the effectiveness of online health interventions in changing behavior including smoking and alcohol use [18-20], and it is likely that in the years to come this will become a primary mode of intervention delivery. To our knowledge, however, there are no existing interventions to reduce the risk of AD delivered over the Internet.

## Methods

### Study setting and design

The BBL project is a 12-week, single-blind randomized control trial of a behavior change intervention targeting established risk factors for AD delivered to cognitively healthy adults aged 50 to 60 either exclusively online or as a combination of online and small group meetings. These two groups are being compared to an active control group receiving weekly email links to relevant health information. The study is being conducted in Canberra, Australia.

### Participants

Recruitment for this study is currently ongoing. Participants are being recruited from the community via advertising in local newspapers and radio, as well as by distributing fliers in community health centers, community clubs, and through word of mouth. Participants who call the study number are added to a database of those expressing an interest in the study. Potential participants are then contacted by phone or email and are provided with additional details regarding the study and with a brief set of questions to establish whether basic inclusion criteria (see below) are met. Participants are also asked at this point to consent to undergo further screening in the form of two brief phone interviews to further establish the presence of inclusion or exclusion criteria.

### Inclusion criteria

Study prerequisites are that participants are aged 50 to 60, reside in the Australian Capital Territory or surrounding areas of New South Wales, have access to a computer and Internet connection at home, and are fluent in English. To be eligible for the study, participants are required to meet a minimum of three of the following risk factors for AD: formal educational attainment at high-school level or less, sedentary lifestyle, overweight or obese body mass index (BMI), low consumption of fish, low cognitive or social engagement, as well as a history of diabetes, hypertension, high cholesterol, mild to moderate traumatic brain injury, smoking, or depression. Participants are required to be able to attend the Centre for Research on Ageing, Health, and Wellbeing at baseline and after 24 weeks for face-to-face evaluations.

### Exclusion criteria

Participants are not eligible to enroll in the trial if they have a history of neurological or psychiatric conditions likely to substantially affect cognition (for example, recent stroke, epilepsy, schizophrenia), sensory deficits or mobility limitations that would prevent or substantially restrict the delivery of the assessment or intervention (for example, uncorrected substantial loss of hearing or vision, severe physical disability), as well as other significant health problems (for example, recent cardiovascular event, renal failure, treatment for cancer). Participants are also required to obtain a score greater than 24 on the TELE instrument (a phone-based assessment of mental status) [21] to exclude the presence of global cognitive impairment.

### Phone interviews

Two brief phone interviews conducted by research assistants with graduate psychology training using a written protocol are being conducted with participants as part of the screening process. The first interview focuses on past and present medical conditions that form the study’s inclusion and exclusion criteria, while the second interview focuses on lifestyle factors. Each of the phone interviews generally lasts approximately 10 minutes.

### Sample size calculations

Sample size calculations were estimated using G*Power (version 3.1.3)(Available at: University of Dusseldorf available at http://www.psycho.uni-duesseldorf.de/aap/projects/gpower/.) and were based on medium effect sizes found for multidomain lifestyle interventions for the primary prevention of cardiovascular disease (CVD) [22] due to the lack of published trials on dementia risk reduction. To detect a medium effect in a 3-group design (1:1:1), with a 5% risk of type 1 error (α) and 80% power, a total sample size of 159 persons is required. A medium effect (0.5 standard deviation) on the Australian National University AD Risk Index (ANU-ADRI) is 4.25 points on the scale as described previously [8]. This figure is derived from the pooled standard deviation of the ANU-ADRI from three cohort studies with combined N of 4301; the Rush Memory and Aging Study, the Kungsholmen Project, and the Cardiovascular Health Study. To account for attrition, a baseline sample of 180 is being recruited.

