### Statistical analyses

Statistical analyses will be based on an intention-to-treat approach. Recent commentary on the best practice for dealing with missing data in RCTs suggests that multiple imputation and Mixed Models are effective approaches and superior to the commonly used techniques like ‘last observation carried forward’ for missing data [25,26]. We plan to use Mixed Models. We hypothesize that BBL + FF > BBL > ACON. The hypothesis that BB + FF > BBL is based on research [27] showing that social milieu and personal contact with researchers are associated with better outcomes in online interventions. There is no empirical evidence on which to base the hypothesis that BBL + FF > BBL in relation to dementia risk reduction per se, due to lack of published data. Results will be exploratory because there are no previous findings in the literature to confirm. There is random allocation to groups so we do not plan to adjust for baseline variables in the primary analysis. In sub analyses we will adjust for baseline measures such as compliance in completing the online modules (in the BBL and BBL + FF groups) by including the number of online modules completed as a fixed effect.

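### The total of 159 matches an omnibus three-group test at Cohen's f = 0.25, but the text equates its medium effect with 0.5 SD (4.25 points), for which that calculation does not support 80% power

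*Protocol article*

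**What the plan says.** Under Sample size calculations, the protocol article names G*Power as the software. For a medium effect across three equally sized arms, it gives this target: "with a 5% risk of type 1 error (α) and 80% power, a total sample size of 159 persons is required". It then puts the effect on the scale of the primary outcome: "A medium effect (0.5 standard deviation) on the Australian National University AD Risk Index (ANU-ADRI) is 4.25 points on the scale". The scale figure comes from external data: "This figure is derived from the pooled standard deviation of the ANU-ADRI from three cohort studies with combined N of 4301". Recruitment is set above the computed total: "To account for attrition, a baseline sample of 180 is being recruited".

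The section does not name the test, the effect-size index entered in the software, the sidedness or any multiplicity correction.

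Under Statistical analyses, the hypothesis is an ordering of the three arms, "We hypothesize that BBL + FF > BBL > ACON", and the method is given as "We plan to use Mixed Models". That section also says that the primary analysis will not adjust for baseline variables and that results will be exploratory.

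**The concern.** The section uses one term, a medium effect, for the effect behind the 159 and for the 0.5 SD difference. A reader will therefore take it that 159 participants give 80% power to detect 4.25 points.

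Medium means 0.25 on Cohen's f, which measures the spread of several means, and 0.5 on Cohen's d, which measures the distance between two means. The two agree when there are two equal groups, where f = d/2. They do not agree with three. If 159 was computed on f and then described on d, the stated power belongs to a larger difference than the one named.

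This is the only power statement for the primary outcome. It is what readers will use to judge what size of difference the trial could be expected to detect.

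**Working it through.** **Inputs from the article:** three arms, 1:1:1; alpha 0.05; power 80%; total 159, so 159/3 = 53 per arm; 180 recruited, so 60 per arm; 0.5 SD = 4.25 points, so SD = 4.25/0.5 = 8.5 points.

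**Step 1. Reproduce 159.** Omnibus one-way ANOVA, k = 3, noncentrality λ = f²N, degrees of freedom 2 and N − 3.
- f = 0.25, N = 156: power 0.797.
- f = 0.25, N = 159: λ = 0.0625 × 159 = 9.94, power 0.805.

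So 159 is the smallest balanced total that reaches 80%, an exact match.

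**Step 2. Can 159 come from 0.5 SD?** Totals for 80% power, for the readings tried:

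| Reading of 0.5 SD | Total N |
|---|---|
| Pairwise t-test, two-sided 0.05 | 3 × 64 = 192 |
| Pairwise t-test, one-sided 0.05 | 3 × 51 = 153 |
| Omnibus F, largest difference 0.5 SD, third arm midway | 237 |
| Omnibus F, largest difference 0.5 SD, two arms equal | 177 |
| Omnibus F, 0.5 SD step between adjacent arms (f = 0.408) | 63 |
| Omnibus F, f = 0.5 | 42 |

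None gives 159.

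**Step 3. Convert between d and f in three equal groups.** f is the standard deviation of the three means (divisor 3) over the within-group SD. With a largest difference of d:
- Third arm midway: f = d/√6 = 0.5/2.449 = 0.204.
- Two arms equal: f = d√2/3 = 0.5 × 0.4714 = 0.236.

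If 0.5 SD is the largest difference, f cannot reach 0.25. Conversely, f = 0.25 needs a largest difference of 0.25 × 3/√2 = 0.53 SD (× 8.5 = 4.5 points) to 0.25 × √6 = 0.61 SD (5.2 points).

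**Step 4. Power for 4.25 points.**

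Pairwise, two-sided 0.05, no multiplicity correction, one time point; noncentrality d√(n/2):
- n = 53: 0.5 × √26.5 = 2.57, power 72.2%.
- n = 60: 0.5 × √30 = 2.74, power 77.5%.

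Omnibus F, with 0.5 SD as the largest difference:

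| Third arm | N = 159 | N = 180 |
|---|---|---|
| Midway (f = 0.204) | 62.1% | 68.0% |
| Equal to one of the others (f = 0.236) | 75.4% | 80.8% |

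**Step 5. Difference detectable with 80% pairwise power at 53 per arm:** d = 0.549, and 0.549 × 8.5 = 4.67 points.

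**Step 6. What baseline adjustment could do.** With baseline to follow-up correlation ρ (an assumption; the article gives none), adjusting for baseline multiplies the residual variance by 1 − ρ². Pairwise power reaches 80% when 53/(1 − ρ²) ≥ 64, that is ρ ≥ √(1 − 53/64) = 0.415. If a Bonferroni correction over three contrasts were applied, 86 per arm would be needed, so ρ ≥ √(1 − 53/86) = 0.62.

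**The case against.** **The test and f are inferred.** This stands as a limit: the article names neither. The match is exact, however, and no 0.5 SD reading tried gives 159.

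**A one-sided test would have enough power.** At 53 per arm it has 81.9%. But no one-sided test is stated, and that route leads to 153.

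**0.5 SD might be the step between adjacent arms.** The article does not say which contrast it means. On that reading omnibus power at 159 is 99.7%, but only 63 participants would be needed, and each adjacent comparison still has about 72%.

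**The planned analysis is a mixed model with the ANU-ADRI measured at baseline, 12 and 24 weeks.** This is the strongest objection, and it stands. A reader might infer that the trial is underpowered for 4.25 points. The article does not support that, because power under the planned model depends on a correlation it does not give. For one follow-up minus baseline at 53 per arm, pairwise power is 58%, 72% and 81% at correlations of 0.3, 0.5 and 0.6. For the mean of both follow-ups minus baseline, assuming equal correlations and the same effect at both visits, it is 70%, 84% and 91%. The planned analysis may fall on either side of 80%. The sample size paragraph uses no such correlation, so this possibility does not rescue the statement made there.

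**Lower power figures can be produced.** A Bonferroni correction over three contrasts gives 56%, and BBL + FF against BBL with BBL midway gives about 25%. The article commits to neither the correction nor the midway position, so these are not properties of the plan. The 62% omnibus figure likewise assumes a midway arm and is only one end of a range.

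**The trial is a self-described pilot with exploratory results.** This lowers the weight of the point, but the stated number and the stated effect still disagree.

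**Conclusion.** The point holds as an effect-size mislabel. The arithmetic behind 159 is sound for f = 0.25 in an omnibus test. It does not support 80% power for 0.5 SD, the effect described in the next sentence. The shortfall is moderate: about 8 percentage points for a pairwise comparison at 53 per arm, and between 2 and 3 points with no attrition. On the omnibus test at 159 it is about 5 to 18 points if 0.5 SD is the largest difference.

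These figures rest on the article's SD of 8.5 points, a two-sided 0.05 level without multiplicity correction, and a single-time-point comparison. The finding is that the stated calculation does not deliver the stated power for the stated difference. It does not show that the design cannot reach 80%, or that more participants must be recruited.

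**What to change.** Rewrite the power statement under Sample size calculations, for example: a total of 159 gives 80% power for f = 0.25 in an omnibus three-group F test at alpha 0.05. For a 4.25-point (0.5 SD) difference between two arms at 53 per arm, single-time-point power is 72% (two-sided 0.05, no multiplicity correction), and the difference detectable with 80% power is 4.67 points. The authors should confirm from their G*Power record that the omnibus test and f = 0.25 were what they entered. The cost is one corrected paragraph and a less favourable power figure; enrolment is unchanged.

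A separate option is to adjust the primary analysis for baseline ANU-ADRI, which is already collected. That would bring pairwise power to about 80% if the baseline to follow-up correlation is about 0.42 or more. The correlation is an assumption. The step would also change the statement under Statistical analyses that the primary analysis is not adjusted for baseline variables. At 0.42 it would not suffice under a multiplicity correction: with Bonferroni over three contrasts, power is about 66%. The correction to the sample size paragraph is needed whether or not this option is taken.

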### Assessments

Table 1 summarizes the primary and secondary assessment measures and the assessment schedule.

**Table 1 T1:** Assessment measures at the baseline, post-intervention, and follow-up evaluations

**Assessment measure**	**Baseline**	**12 weeks**	**24 weeks**
Questionnaires			
ANU-ADRI^a^	X	X	X
Dementia literacy questionnaire^a^	X	X	X
Motivation questionnaire^a^	X	X	X
Cognitive measures			
Logical memory	X		X
RAVLT	X		X
RCFT	X		X
COWAT (FAS)	X		X
Category fluency (animals, boys, category switching)	X		X
WTAR	X		X
Digit span	X		X
Digit-symbol matching^a^	X		X
Trials A + B^a^	X		X
Physical evaluation			
Blood pressure	X		X
Height, cm	X		X
Weight, kg	X		X
Hip to waist ratio	X		X
Forced expiratory volume	X		X
Forced vital capacity	X		X
Quadriceps strength	X		X
Blood tests (optional)			
Lipids	X		X
ALT	X		X
HbA1c	X		X
Renal function	X		X

^a^Administered online on the trial website.

ALT, alanine aminotransferase; ANU-ADRI, Australian National University Alzheimer’s Disease Risk Index; COWAT, Controlled Oral Word Association Test; Hb, hemoglobin; RAVLT, Rey Auditory Verbal Learning Test; RCFT, Rey Complex Figure Test; WTAR, Wechsler Test of Adult Reading.

#### Primary outcome

The primary outcome measure is the ANU-ADRI [8]. The ANU-ADRI was developed following a synthesis of meta-analyses of various risk factors for AD reported in the literature. The questionnaire covers several modifiable risk factors and is based on self-report.

